### Patient and public involvement

This proposal has been developed collaboratively with our PAG, and their comments and suggestions about the format of the intervention and parent/carer materials have informed for both the intervention and the final design of the feasibility study. The PAG will meet throughout the study, twice per year, allowing the investigators to report on progress of the study and discuss issues that arise during the study. PAG members will input in all the material for parents/carers as and when these are developed, including the patient information sheet, intervention materials and the topic guide for interviews. We have also formed a CAG, involving GPs and practice nurses, to assist with developing and refining the intervention. They will meet once in person and then contribute by Skype or email to refine GP/nurse information and intervention delivery. We will work closely with our advisory groups, particularly during the first 9 months of this work package.

## Ethics and dissemination

### Burden

As the feasibility trial is assessing a behavioural intervention and participants are attending for a routine consultation with a clinician, there are no risks to the participants taking part in this study. Children will not be randomised to receive a medication or intervention, and no treatment will be withheld. Further clinical management will be decided on by the patient's clinician, as it is the choice of the recruiting clinician as to whether the participants are treated or not for their cough.

The main burden will be the additional time associated with participating in the study. This has been reduced to a minimum by only asking some short concise questions during their routine consultation, and questions about the child’s recovery, treatment and healthcare resources at follow-up.

The intervention itself will be assessed as to whether the components of the intervention could potentially increase hospitalisations by virtue of reducing antibiotic prescribing, and so families will be asked weekly whether their child has been hospitalised in the preceding 7 days via the weekly phone call.

### Adverse events and serious adverse events

Any unexpected adverse events (AEs) defined as ‘any untoward medical occurrence in a trial participant’ and serious AEs (SAEs)—defined below—will be monitored by the trial team and reviewed at monthly management group meetings.

From our earlier work, we anticipate that approximately 1% (2–4 children) of children presenting with RTI will be hospitalised. We will ask recruiting practices to inform the trial coordinator of any unexpected SAEs that occur during the child's participation in the trial.

The principal investigator and trial coordinator will assess the nature of the SAE for seriousness, causality and expectedness. Following the initial report, follow-up data may be requested by the trial coordinator. All reports will be submitted to the DMC for scrutiny of our ongoing findings. Where the SAE is both related and unexpected, the trial coordinator will notify the main REC, the sponsor of the trial, and its research governance office within 15 days of receiving notification of the SAE.

As one of the outcomes for the trial is hospitalisation, we do expect some participants to be admitted to hospital due to a deterioration of their underlying illness, for example, pneumonia, empyema and deteriorating bronchiolitis. At follow-up, parents/carers will be routinely asked if they have reconsulted for their child's illness and if so, where this was done. In addition, whether the child has been hospitalised will also be asked. Once a child has been identified as hospitalised, either in the ED or on a ward, the standard SAE process will be followed as described above. All expected SAEs will be reported as part of the outcome to the trial.

### Definition of a SAE

This is any untoward and unexpected medical occurrence or effect that: results in death; is life-threatening (refers to an event during which the participant was at risk of death at the time of the event, and not to an event that might have caused death had it been more severe in nature); requires hospitalisation or prolongation of existing hospitalisation; or results in persistent/significant disability or incapacity.

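### The SAE definition admits only unexpected events, which contradicts the SAE process and lets practices leave unreported the admissions named as the trial's possible harm

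*Protocol article*

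**What the plan says.** All places are in the protocol article, under Ethics and dissemination unless stated.

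- **Definition of a SAE.** The definition starts "This is any untoward and unexpected medical occurrence or effect that" and continues with the usual seriousness criteria, one of which is that the event "requires hospitalisation or prolongation of existing hospitalisation".
- **Adverse events and serious adverse events: practices.** "We will ask recruiting practices to inform the trial coordinator of any unexpected SAEs that occur during the child's participation in the trial".
- **Same section: assessment.** The principal investigator and trial coordinator assess each SAE for seriousness, cause and expectedness. All reports go to the DMC. Events that are both related and unexpected are notified to the ethics committee, the sponsor and its governance office within 15 days.
- **Same section: hospitalisation.** The authors write that "we do expect some participants to be admitted to hospital due to a deterioration of their underlying illness", giving pneumonia, empyema and worsening bronchiolitis as examples. They add: "Once a child has been identified as hospitalised, either in the ED or on a ward, the standard SAE process will be followed". SAEs that were expected are to be reported with the trial outcomes.
- **Burden.** "The intervention itself will be assessed as to whether the components of the intervention could potentially increase hospitalisations by virtue of reducing antibiotic prescribing", and for that reason families are asked about hospitalisation every week. Earlier in the same section: "there are no risks to the participants taking part in this study".
- **Abstract and Data collection (Methods and analysis).** Parent contact is weekly until the illness resolves, or up to 8 weeks. The medical record review takes place 2 months after recruitment and covers the 30 days after the recruiting consultation.

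**The concern.** In a safety process, seriousness normally decides whether an event is an SAE, and expectedness decides only how fast and to whom it is escalated. Here expectedness has been moved into the definition as well, although the process still treats it as a later step. The two sections then give different answers to a basic question: is an admission for worsening RTI an SAE or not?

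The ambiguity falls on the event that matters most. The intervention is meant to reduce antibiotic prescribing, and the harm the protocol itself names is that less prescribing might lead to more hospitalisation. That is the class of event declared expected. The recruiting practice holds the record in which hospitalisations will later be looked up, and its notification does not depend on a parent answering a call. Yet its instruction is confined to unexpected events. At stake is how promptly and completely the DMC sees these admissions while recruitment continues.

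**Working it through.** **1. The rules side by side, applied to one case.** Take a recruited child admitted to a ward with pneumonia after the RTI worsens.

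| Rule | Result for this child |
|---|---|
| Seriousness criterion | Met: hospitalisation |
| Expectedness as declared in the adverse events section | Expected |
| SAE under the definition (untoward and unexpected) | No |
| Practice asked to notify (unexpected SAEs only) | No |
| SAE process once the admission is identified | Yes |
| Reported with the outcomes as an SAE that was expected | Yes |

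The third and fourth rows cannot be reconciled with the last two.

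**2. Internal logic.** The adverse events section opens by saying that SAEs are as defined below, so the definition governs the process. If every SAE is unexpected by definition, three parts of that process have nothing to act on:
- the assessment of expectedness;
- the *unexpected* half of the 15-day criterion;
- the category of SAEs that were expected.

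The process makes sense only if *unexpected* is not part of the definition.

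**3. What remains if the practice follows its instruction.** Two routes can still identify the admission.
- *Weekly parent contact.* This is prompt when the parent responds. Attrition and retention are themselves feasibility outcomes (Outcome measures), so full response cannot be assumed.
- *Record review.* This is independent of the parent but late. Taking 2 months as about 60 days (an assumption), an admission on day *d* of the 30-day window is found about 60 − *d* days later: about 60 days if *d* = 0 and about 30 days if *d* = 30. The 15-day period runs from receipt of notification, so late identification does not breach it but moves its start back.

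**4. How many events.** The plan's figure is "approximately 1% (2–4 children) of children presenting with RTI will be hospitalised". At the minimum sample of 300 (Sample size), 0.01 × 300 = 3. The stated ends are 2/300 = 0.67% and 4/300 = 1.33%, so the figure reproduces as about 1% around 300. At the upper target of 500 (Methods and analysis), 0.01 × 500 = 5. The 95% binomial ranges at 1% are 0 to 7 events for 300 children and 1 to 10 for 500. These counts bound the extra practice reports from admissions; they are not evidence of an error.

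**The case against.** The strongest reply is that the specific rule on hospitalisation overrides the loose definition. Every child identified as hospitalised enters the SAE process, all reports go to the DMC, families are asked weekly, and hospitalisation is also an outcome collected from records. A child admitted because the RTI has worsened has usually not recovered, so weekly calls would normally still be running. Most of this stands. A reader might infer from the definition that these admissions escape SAE reporting altogether, and the documents do not support that. What the reply leaves untouched is that the overriding rule starts only once an admission has been identified, and the practice route to identification is the one that has been narrowed.

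Three other inferences are tempting but do not hold.
- *The 2–4 count is wrong because the target is 300 to 500.* It fits the 300 minimum, differs by one child at each end from 3 to 5, and no alert or stopping threshold is tied to it.
- *The trial lacks power to show an increase in hospitalisation.* No hypothesis test on hospitalisation is planned. The Burden sentence leads into weekly questioning, which is monitoring, and low power for rare harms is inherent in a feasibility trial.
- *The 1% may leave out ED attendance.* The earlier work behind the figure is not shown, so this is conjecture.

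**Conclusion.** The contradiction between the SAE definition and the SAE process is real and lies in the current text. Its practical effect is limited: one of several reporting routes, practice notification, is closed for the harm that the protocol names. The cost is timeliness, chiefly for families who stop responding, where identification could wait for the record review, roughly 30 to 60 days after admission on the assumption above. At the protocol's own rate only a handful of children would be affected in total. No estimate, sample size or planned analysis changes.

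The conclusion assumes that practices follow their instruction as written and that the full protocol does not give them a wider one. Separately, the flat statement in Burden that participation carries no risk does not fit with the concern stated there about more hospitalisation, and the two need to be made consistent.

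**What to change.** 1. Remove *and unexpected* from the SAE definition, so that seriousness alone decides whether an untoward event is an SAE.
2. Remove *unexpected* from the instruction to practices, so that they notify all serious events, including admissions for deterioration, and these go to the DMC with the other reports.
3. Use expectedness only where the adverse events section already uses it for escalation: deciding, together with relatedness, whether the 15-day notification applies. Keep reporting expected SAEs with the outcomes.
4. Reword the no-risk statement in Burden so that it agrees with the hospitalisation concern in the same section.

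The cost is a few words of protocol text, a matching change to the practices' instructions, and a handful of extra practice reports: about 3 to 5 admissions at the stated 1%. Some will duplicate what parents report, which is useful in a trial that already plans to compare parent-reported hospitalisations with the medical record.

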### Study sponsorship

The University of Bristol will act as sponsor for study. Delegated responsibilities will be assigned to the Universities and NHS trusts taking part in this study. The study is open to inspection and audit by the University of Bristol under its remit as sponsor.

### Dissemination

The outputs from this research will comply with the TARGET Programme's publication policy. All results will be described in the Programme's final report and as papers in peer-reviewed journals. Papers will be produced to describe the findings from this feasibility study, and results will be presented at national and international research conferences. A summary of the findings will be sent to participating practices (and this will be available to their patients) on completion of the CHICO study.
